# Effectiveness of steroids versus placebo in preventing upper airway obstruction after extubation in critically ill children: rationale and design of a multicentric, double-blind, randomized study

**DOI:** 10.1186/s13063-020-4218-2

**Published:** 2020-04-19

**Keywords:** Steroids, Dexamethasone, Stridor, Upper airway obstruction, Children, Extubation

## Abstract

**Background:**

Post-extubation upper airway obstruction (UAO) is a frequent complication causing stridor and respiratory distress, which occasionally require reintubation, thereby increasing morbidity and mortality rates. Contradictory results have been obtained in studies assessing the effectiveness of steroids in preventing post-extubation UAO, and the available evidence is limited. We designed a multicentric randomized, placebo-controlled study to explore the effectiveness of dexamethasone in preventing post-extubation UAO in children.

**Methods:**

A multicentric, prospective, double-blind, randomized, placebo-controlled, phase IV clinical trial has been designed. The sample will include pediatric patients who are between 1 month and 16 years of age and who have been intubated for more than 48 h. Patients who have airway disorders or who have received steroids within the previous seven days will be excluded. Patients will be randomly assigned to receive either placebo or a therapy with dexamethasone 0.25 mg/kg every 6 h to be started 6 to 12 h prior to extubation (to a total of four doses). Randomization will be performed at a 1:1 ratio. Follow-up of patients will be carried out for 48 h after extubation. The main objective of this study is to access the reduction in the incidence of moderate to severe UAO symptoms following extubation. Secondary objectives include assessing the decrease in the incidence of reintubation, evaluating the use of additional therapies for UAO, and monitoring potential side effects of dexamethasone.

**Discussion:**

The results of this study will contribute to the existing evidence on prophylaxis for post-extubation airway obstruction.

**Trial registration:**

EudraCT identifier: 2009–016596-30. Registered on May 11, 2010.

## 1. Background

Critically ill pediatric patients frequently require endotracheal intubation. Post-extubation upper airway obstruction (UAO) is a common complication that affects up to a third of patients who require endotracheal intubation [1–3].

Owing to the small diameter of their airways, laryngeal edema is more frequent and severe in children than in adults. Indeed, this type of edema in children affects the subglottal region more frequently than the glottal region [2, 4]. Signs of airway obstruction include stridor and respiratory distress, which require reintubation in 6–13% of patients [1–3].

Risk factors related to post-extubation UAO include underlying respiratory or neurological disease, prolonged intubation (more than 36–48 h), reintubation, a young age (≤24 months of age), or infant weight of less than 5 kg [1, 2].

The obstruction of the upper airway has significant effects on the evolution of the patient. This complication may increase morbidity and mortality, length of hospital stay, duration of mechanical ventilation, and health care–related costs, especially when the patient requires reintubation [1, 2, 5, 6].

Steroids are among the most widely used therapies for post-extubation UAO, as they have anti-inflammatory effects, thereby reducing the risk for laryngeal edema and airway obstruction. A range of steroids such as hydrocortisone, methylprednisolone, and dexamethasone have been used for the prevention and management of post-extubation UAO [4, 7]. Contradictory results have been obtained in studies assessing the effectiveness of steroids in preventing post-extubation UAO [5–10].

A recent meta-analysis [7] of studies in adult patients with or without UAO risk factors receiving different regimens of steroids showed that steroids reduce the incidence of upper airway complications and reintubation in high-risk patients.

Studies in pediatric patients are based on widely heterogeneous samples of patients and doses and timing of prophylactic therapy ranging from 1 h to 24 h prior to extubation [4, 7].

In studies on the use of dexamethasone in children, a variety of regimens have been used versus placebo. Some authors report a decrease in the incidence of stridor [5, 8], whereas two studies show a reduction in the incidence of reintubation [8, 9]. A study in neonates concluded that dexamethasone reduced the risk for reintubation [10]. In contrast, this benefit has not been proven in other studies in children [11] and neonates [12].

Baranwal et al. [3] compared two regimens in high-risk pediatric patients: starting dexamethasone therapy 6 h versus 24 h before extubation. The authors found that the 24-h regimen, as compared with the 6-h regimen, significantly reduced the incidence of UAO.

A Cochrane’s systematic review [4] concluded that the effectiveness of steroids in preventing UAO in children has not been sufficiently demonstrated, and further studies are needed to assess its potential benefits, especially in high-risk patients.

In light of the lack of consistent evidence, we designed a randomized study to compare the effectiveness of dexamethasone versus placebo in the prevention of post-extubation UAO in high-risk pediatric patients (>48 h intubated).

The main objective of this study is to explore whether dexamethasone is effective in preventing and reducing the severity of UAO symptoms in critically ill children versus placebo. Secondary objectives include investigating whether dexamethasone reduces the incidence of reintubation and evaluating the potential secondary effects associated with this medication.

## 2. Methods

### 2.1. Study design

This is a multicentric, prospective, double-blind, randomized, placebo-controlled, phase IV clinical trial. Five pediatric intensive care units of hospitals in Spain will participate in the study. The study protocol was developed in accordance with the Standard Protocol Items: Recommendations for Interventional Trials (SPIRIT) checklist (Additional file 1). In May 2010, the study was registered with the European Clinical Trials Register (number 2009–016596-30) under the name “Steroids in the prevention of upper airway postextubation complications in critically ill children”.

### 2.2. Study population

The sample will include children (between 1 month and 16 years of age) who are admitted to the intensive care unit and who require intubation for more than 48 h, regardless of their condition. Patients with airway malformations, suspected or confirmed croup syndrome, tracheitis, or epiglottitis and those who had previously undergone any surgery involving upper or lower airway will be excluded. Other exclusion criteria are the administration of steroid therapy within the previous seven days, patients who had a previous extubation failure during the stay, or refusal to participate in the study.

### 2.3. Recruitment

Study candidates will be identified by a study physician, who will explain the study to parents or guardians. Written informed consent will be obtained from parents or guardians prior to inclusion in the study. A CONSORT (Consolidated Standards of Reporting Trials) flow diagram is shown in Fig. 1.

**Fig. 1 Fig1:**
[figure not shown]
CONSORT (Consolidated Standards of Reporting Trials) flow diagram

### 2.4. Randomization and masking

Patients will be assigned to one of the two therapy groups on a 1:1 ratio by simple randomization using a randomization table on EPIDAT 3.1 (Epidat: software package for epidemiological data analysis. 2006. Consellería de Sanidade, Xunta de Galicia, España; Organización Panamericana de la Salud; Universidad CES, Colombia). The coordinating center will send a table for sequential randomization of patients. This table will contain the number of the medication that has been assigned to each patient. The treatment group will not be detailed in the randomization table. This table will include a number of a reserve medication for use in case of deterioration or loss or if the drug is rendered unusable. The pharmacy unit of the coordinating center will send treatment-arm assignments labeled and blinded as established in the randomization table for each center.

The labeling and blinding of medication kits will be performed by the pharmacy unit of the coordinating center, which will keep an open record of these kits and their composition. This record will be coded and stored by the coordinating center pharmacist responsible for the labeling and submission of samples.

If severe or unexpected adverse events related to the medication appear the principal investigator will require the appointed pharmacist to unblind the codes identifying the sample. The principal investigator will be informed so that timely action can be taken. The unblinding of any code will be recorded by the pharmacist responsible for sample blinding.

### 2.5. Intervention

The treatment group will receive intravenous 0.25 mg/kg per dose (to a maximum of 8 mg) every 6 h for a total of four doses. The first dose will be administered between 6 and 12 h prior to extubation. The placebo group will be administered saline 0.9%. The study medication will have the same aspect and characteristics as those of placebo and both will be administered in the same way. Dose adjustment, discontinuance, or reinitiation of treatment will not be allowed. Inspections will be performed to ensure that the treatment is being administered adequately.

### 2.6. Data collection and assessment of efficacy

On inclusion, demographic (age, sex, and weight) and clinical data will be collected as follows:
Diagnosis (six diagnostic groups will be established): surgery, lower airway obstruction, neurological disease, sepsis, trauma, and other diagnosis.Assessment of severity: the clinical status of the patient will be assessed by using Pediatric Index of Mortality 2 (PIM2), Pediatric Risk of Mortality III (PRISM 3), and Pediatric Logistic Organ Dysfunction (PELOD) scores prior to extubation.Size and type of endotracheal tube (cuffed or uncuffed).Route of intubation (oral or nasal).Previous need for endotracheal tube replacement.Previous airway endoscopies.Respiratory infection confirmed by endotracheal aspirate culture.Presence of blood in endotracheal aspirate.Duration of endotracheal intubation prior to extubation (in days).

The primary endpoint is the reduction of the incidence of moderate to severe UAO symptoms within 48 h after extubation. Moderate to severe UAO symptoms will be considered if stridor or a Taussig score of more than 5 is present. The secondary endpoints are the presence of reintubation and the potential secondary effects associated with dexamethasone.

A record of the following variables will be kept at 15 min and 1, 2, 6, 12, 24, and 48 h after extubation:
UAO Taussig score [13], a clinical scoring system for the assessment of UAO severity; evaluating stridor, retractions, inflow of air into the lungs, cyanosis, and consciousness (Table 1). Presence of inspiratory stridor.Need for and frequency of additional therapies for respiratory distress: adrenaline or nebulized budesonide, intravenous steroids, heliox, or non-invasive ventilation.Hemodynamic (blood pressure and heart rate) and respiratory (peripheral oxygen saturation and respiratory rate) parameters.Arterial partial pressure of carbon dioxide (pCO_2_) and partial pressure of oxygen (pO_2_) and glycemia. Blood samples will not be routinely collected; they will be drawn only for clinical purposes.Need for reintubation, time point, and cause.Presence of digestive bleeding.Occurrence of infection.

**Table 1 Tab1:** SPIRIT (Standard Protocol Items: Recommendations for Interventional Trials) Schedule of Events Timeline: enrolment, assessment of safety, assessment of efficacy, and dispensing of the medicine

Tests	Screening	First visit prior to extubation	Visits 2 to 8

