**Deliveries of medication**			
Randomization and dispensing of the medication		X	X
Contact with the randomized-dispensing center	X	X	X

Visits 2 to 8, respectively: 15 min, 1 h, 2 h, 6 h, 12 h, 24 h, and 48 h after extubation

The timing of parameter recording is shown in Table 2.

**Table 2 Tab2:** Modified Taussig score

	Score			
	0	1	2	3
Clinical parameters				
Color	Normal	Normal	Normal	Cyanotic
Air entry	Normal	Mildly diminished	Moderately diminished	Substantially diminished
Retractions	None	Mild	Moderate	Severe
Level of consciousness	Normal	Restlessness if disturbed	Restlessness at rest	Lethargy
Stridor	None	Mild	Moderate	Severe (or no stridor if severe obstruction)

Upper airway obstruction is considered mild if score is less than 5 points, moderate-severe with at least 5 points. Modified Taussig score [13]

All interventions that patients require for their treatment are allowed but those that could affect the upper airway (respiratory tract infections, reintubations, etc.) will be recorded and will be taken into account in the statistical analysis.

For each participating center, a co-investigator will be appointed to verify the correct adherence to the study protocol, checking in every 8-h shift to confirm that the medication is prescribed in the treatment and that it has been administered. This investigator will also be responsible for complete follow-up of every patient.

A monthly communication newsletter regarding recruitment activity will be sent by email to all researchers. In this newsletter, researchers will also be encouraged to continue recruiting.

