### 2.7. Evaluation of safety

The occurrence of adverse events from inclusion to study completion will be recorded for all patients. All patients, including those who discontinue their participation in the study, will be monitored until hospital discharge. Severe adverse events during hospital stay will be reported to the study coordinator and promotor. If severe adverse events occur, follow-up will be performed until remission or until a diagnosis is made and its association with the study medication is established.

A severe adverse event is defined as any adverse event that the patient’s treating physician considers to require treatment on the basis of the characteristics and clinical status of the patient. Severe hyperglycemia is any glycemia greater than 200 mg/dL that persists for more than 6 h or physicians consider to require treatment on the basis of the clinical status of the patient (or both).

Any unused medication will be disposed of in accordance with the protocol established by the pharmacy unit in collaboration with the unit of environmental management of the coordinating center, in compliance with ISO 14.001. Upon study completion, any unused or partially used medication will be sent back to the coordinating center.

Sample size

The estimated incidence of moderate to severe UAO symptoms is approximately 33% [1–3]. We consider a clinically relevant result to be a 50% reduction in the incidence of moderate to severe UAO symptoms in the treatment group.

To calculate the minimum sample size, a two-sample two-proportion two-tiled comparison test was used, and arcsine was used for the approximation for proportions (Cohen’s method). To detect a 50% reduction of incidence (33% UAO symptoms proportion in the placebo group and 16% expected proportion in the treatment group; that is, Cohen’s h effect size = 0.4) with 80% statistical power and a 5% significance level, 110 subjects per arm will be needed. A follow-up loss rate of 10% has been estimated.

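### The primary event is defined inconsistently: section 2.6 counts ungraded stridor or a Taussig score above 5, while Table 2 puts moderate-severe obstruction at 5 points or more and gives mild stridor 1 point

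*Protocol article*

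**What the plan says.** Section 2.6 states: "The primary endpoint is the reduction of the incidence of moderate to severe UAO symptoms within 48 h after extubation". It then gives the event rule: "Moderate to severe UAO symptoms will be considered if stridor or a Taussig score of more than 5 is present". No grade of stridor is required. Stridor is recorded twice at each of the seven assessments from 15 min to 48 h after extubation: within the Taussig score, and as a separate item, "Presence of inspiratory stridor".

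Table 2 sets out the modified Taussig score. Stridor is one of five items and is graded 0 (none), 1 (mild), 2 (moderate) or 3 (severe). The footnote reads: "Upper airway obstruction is considered mild if score is less than 5 points, moderate-severe with at least 5 points".

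The abstract describes the main objective as "the reduction in the incidence of moderate to severe UAO symptoms following extubation". The sample-size paragraph uses the same label and plans on "33% UAO symptoms proportion in the placebo group and 16% expected proportion in the treatment group". Nothing in the article says whether section 2.6 or the Table 2 footnote prevails where they differ.

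**The concern.** The trial has one primary comparison, a Z-test on the proportion of children with the event (section 2.8). That proportion needs one event rule. The article attaches the moderate-to-severe label to two rules that conflict in two respects:

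- **Cut-off.** The text requires a score above 5; the table requires at least 5.
- **Stridor.** The text lets stridor of any grade qualify by itself. In the table, mild stridor adds 1 point, and a total below 5 is mild.

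At stake is which children count as events, and therefore what the primary result means. The early-stopping rule in section 2.9 also rests on the incidence of UAO, with no statement of which definition applies.

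**Working it through.** **1. The plan's own sample size.** Inputs from the sample-size paragraph: 33% v 16%, Cohen's h = 0.4, 80% power, two-sided 5%, 10% loss.

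- n = 2 × ((1.960 + 0.842) / 0.4)² = 98.1, so 99 per arm.
- 99 / 0.90 = 110 per arm.

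The stated 110 reproduces. The arithmetic is sound; the open question is which event the 33% describes.

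**2. The two rules side by side.**

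| Child | Section 2.6 | Table 2 footnote |
|---|---|---|
| Isolated mild stridor, total 1 | event | mild |
| Retractions 2 + consciousness 3, no stridor, total 5 | no event | moderate-severe |
| Total 5 with stridor present | event | moderate-severe |
| Total 6 or more | event | moderate-severe |

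**3. Extent of the disagreement.** In Table 2 color can score only 0 or 3, because it is normal in the first three columns. The other four items run from 0 to 3. That gives 2 × 4⁴ = 512 profiles. Stridor is taken as present when its item is 1 or more.

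- *Event in the text, mild in the table* (stridor item at least 1, total at most 4):
  - stridor 1, other items summing to at most 3: 21
  - stridor 2, others at most 2: 10
  - stridor 3, others at most 1: 4
  - sum: 35
- *No event in the text, moderate-severe in the table* (stridor item 0, total exactly 5):
  - color 0, other three items summing to 5: 12
  - color 3, other three summing to 2: 6
  - sum: 18
- Total: 35 + 18 = 53 of 512.

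The disagreement runs both ways, so neither rule is simply a stricter form of the other.

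Table 2 also gives stridor grade 3 to a child too obstructed to produce stridor. If every grade 3 were such a silent case, the 4 profiles above would leave the first group (35 − 4 = 31). The 6 profiles with grade 3 and other items summing to 2 would join the second (18 + 6 = 24). The conflict remains.

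**4. What the 33% refers to.** The sample-size paragraph ties 33% to moderate to severe symptoms and cites references 1–3. Section 1 (Background) cites the same references for a frequency of up to one third for post-extubation UAO, with no severity grade. The article therefore does not settle which definition the planning rate belongs to.

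**5. Why the attachment matters (assumption, not a forecast).** The document gives no event rate under either rule. Keeping a 50% relative reduction and 99 evaluable children per arm, power by assumed placebo rate is:

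| Placebo rate | 20% | 25% | 33% | 40% |
|---|---|---|---|---|
| Power | 50% | 62% | 77% | 87% |

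The 33% column uses an exact halving to 16.5%; the planned 33% v 16% gives 80%.

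**The case against.** The strongest reply is that section 2.6 is the only explicit event rule for the primary endpoint. On this view the Table 2 footnote merely reports the severity bands of a published scale, and a composite of stridor or score was intended. That is possible. It would make section 2.6 the operative rule, but both places would still use one label for different sets of children, and the article's two cut-offs for the same score would still differ. A fuller analysis plan may settle the matter, but it would not remove a contradiction printed in the protocol article.

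Several stronger readings are tempting, and the document does not support them.

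- *Power collapses.* Suppose half of the 33% is isolated mild stridor that dexamethasone leaves unchanged. The comparison becomes 33% v 16.5% + 8.25% = 24.75%, with power of about 25% at 99 per arm. That share is invented, and section 1 reports that some studies found less stridor with dexamethasone. If the endpoint as written is halved, power is 77%.
- *The 33% belongs to another endpoint than the one in section 2.6.* Section 1 gives the same frequency for ungraded UAO, which fits the broad rule at least as well as a graded one.
- *Every child scoring 5 is affected.* A child scoring 5 with stridor present is an event under both rules.
- *The rule will be picked after unblinding.* Nothing in the article suggests this. The text only leaves room for it.

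**Conclusion.** The point stands as an internal inconsistency in the definition of the primary event, covering both the cut-off and whether ungraded stridor qualifies. It changes the classification of 53 of 512 possible profiles, 35 in one direction and 18 in the other, with stridor counted as present when its item is 1 or more. Profiles are not equally likely in practice, so this is not a patient frequency. The number of children affected, the shift in event rate and the change in power cannot be derived from the document. The sample-size calculation itself is correct. This review does not say which cut-off or stridor rule is clinically right; the two places must be reconciled.

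**What to change.** - **One rule.** State the same event rule in section 2.6 and Table 2: one cut-off, and an explicit statement whether stridor alone qualifies and at what grade. If Table 2 is meant only to describe the scale's bands, say so and give the trial event a label that does not clash with them.
- **Who and when.** The sponsor decides blind to allocation and before database lock. The record should note that the data monitoring committee performed an interim analysis in April 2017 (section 3.1) and which definition it used.
- **Sensitivity analysis.** Report the primary comparison under the other reading as well. Both published rules can be computed from the Taussig total and the separate stridor variable, which are due at every post-extubation visit.
- **Planning rate.** State which definition the 33% refers to.
- **Cross-references.** Section 2.6 cites Table 1 for the Taussig score, which is in Table 2, and later cites Table 2 for the timing of assessments, which is in Table 1.

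A compromise such as stridor alone from moderate grade upwards would be a third definition. By the same enumeration it would still differ from Table 2 on 10 + 4 = 14 profiles and from section 2.6 on 21 + 18 = 39. It would also need the item grades, and the article does not say that these are stored.

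The cost is a documented clarification of the primary endpoint during recruitment, with more than 120 children already enrolled. The event rate may also differ from the one planned. Either published rule needs no new data collection.
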